## Methods/design

This study is a cluster-randomised intervention trial in which general practices were allocated either to an intervention group in which nurse-led collaborative care is to be undertaken or to the control group in which usual GP-led care is to be continued. Ethics approval for the project was obtained from Flinders University Social and Behavioural Research Ethics Committee, approval number 4164. Figure 1 shows the flowchart of the TrueBlue study.

**Figure 1 F1:**
[figure not shown]
**Flowchart of the TrueBlue project**.

### Survey forms

#### Patient Health Questionnaire (PHQ-9)

The PHQ-9 questionnaire will be used to measure and monitor depression over time. It is self-administered, suitable for face-to-face and postal responses and for research. Its brevity and reliability as a valid measure of depression severity make it a useful clinical and research tool [17]. The form has nine questions that are simply scored from 0 (no problems) to 3 (problems nearly every day). Each of these assesses various physiological and mood indicators of depression, and are combined to form the total PHQ-9 score. Scores 5–9 indicate mild depression, 10–14 moderate depression, 15–19 moderately severe, and scores above 19 indicate severe depression.

#### SF36 (Version 2)

Health and lifestyle will be measured using version 2 of the SF-36 questionnaire. This questionnaire is a multi-purpose, short-form health survey that provides a profile of health and well-being as well as a psychometrically-based physical and mental health summary measures and a preference-based health utility index [18]. This questionnaire provides a suite of generic measures rather than specific ones, but has proven to be useful in surveys of general and specific populations in differentiating the health benefits produced by a wide range of different treatments.

#### The GP Management Plan (GPMP)

Critical to collaborative care in chronic-disease management is a system that ensures the coordination of care between the GP and other health-care providers and assists patient self-management. This document, the GP management plan (GPMP), was developed by the GGT UDRH in collaboration with each of the practices in the programme. The design of this multi-purpose document enables it to serve the following functions, within the limits of current electronic medical-record applications, with minimum data entry:

• Provide a single template covering T2DM and CHD diagnoses;

• List patient medical history;

• List medication used, including prescribed medication, aspirin and antidepressant use;

• Record physiological risk factors, including blood pressure, weight, height, body-mass index (BMI), waist circumference, microalbuminuria, lipid profile and, for diabetic patients, HbA1c;

• Record lifestyle risks, including smoking, alcohol consumption and exercise regime;

• Record the psychosocial risks and PHQ-9 depression scores, including referrals to and consultations with a mental-health worker;

• Checklist of preventative activities and targets recommended in National Heart Foundation and Diabetes Australia guidelines;

• Individual patient goals, targets and agenda for future consultations;

• List referrals to specialists, allied health and community resources;

• Timetabled recall;

• Help practices complete the requirements to claim Medicare rebates for care planning and diabetes cycle of care; and

• Automatically generate de-identified data for research and audit.

The GPMP includes an office-use summary table containing only data that are relevant to the research. These data are identified only by a unique patient ID number assigned by the patient's practice. No personal details are forwarded to the research team. The patient information in the GPMP office-use summary is listed in the Appendix.

### Sample size

Nine intervention and nine control practices, each with 50 patients, will be required to detect a minimum 2-point reduction in the PHQ-9 score at the 0.05 significance level with 80% power. These patient and practice numbers were determined assuming a change in PHQ-9 with standard deviation of 5.1 as observed in the pilot study [13], a drop-out of no more than 33%, and an intra-cluster correlation of 0.04. Note that detecting a 2-point reduction in the overall PHQ-9 score is a more-stringent requirement than this project's objective of achieving a 50% reduction in that score.

### Practice recruitment

Practices from three regions (Adelaide, inner Melbourne and the NSW Northern Rivers area) were selected to undertake the study. Practices were selected from these regions using a range of criteria, including size and capacity, and assessable electronic medial records capable of generating an electronic registry of patients with CHD or T2DM. Practices also needed to have a PN available to lead the collaborative care.

Information about the study was circulated to these practices to explain the benefits of the True Blue project to their GPs, PNs and practice managers. These were followed up with orientation evenings that provided further detail. GPs who were interested in the project and who were able to guarantee protected time for their PN(s) to undertake the collaborative care were invited to join and their clinics included in the project, until six practices from each of the three regions had been selected.

#### Randomisation

Nine practices were randomly allocated to the intervention group in which nurse-led collaborative care will be undertaken. The remaining nine practices were allocated to the control group in which the usual GP-led care will continue for a period of six months. At the end of this period, the control practices will be invited to implement the practice nurse-led model of collaborative care and to send practice nurses to a training workshop (see below).

### Patient recruitment

Within each general practice, a mailing list of patients with a diagnosis of CHD or T2DM is generated. Patients who are either under 18 years of age or in residential care are excluded from the study. Eligible patients are added to the master list as potential participants in the programme and assigned a unique identification (ID) number. All documentation or data forwarded to the researchers for the patient is identified only by this unique ID number. Personal details of patients, including names and addresses, are retained by the clinic concerned.

An information package is posted from the practice to each of these patients. It includes a standardised personal letter from their GP explaining the study, information brochures, a PHQ-9 questionnaire, and a consent form indicating the patient's willingness to participate in the programme. Each patient is asked to complete and return the PHQ-9 and consent forms. The returned PHQ-9 questionnaire from consenting patients is examined to identify PHQ-9 scores above 5, indicating presence of at least mild depression. These patients are invited to join the study. Patients who do not respond to the first mail-out are sent a reminder letter approximately two weeks later inviting them to participate, with further reminder letters, telephone calls and personal invitations when visiting clinics, until 50 patients have been recruited.

### Inclusion and exclusion criteria

Practices with an electronic-medial-records system capable of generating an electronic registry of patients with CHD or T2DM and with a PN available to lead the collaborative care are eligible to participate. Patients with either T2DM or CHD are eligible to participate, provided that they were over 18 years of age and are not in residential care.

### Practice nurse training workshop

A two-day training workshop was organised for the PNs from the intervention practices to prepare them for enhanced roles in nurse-led collaborative care. This workshop introduced the rationale of the collaborative care model before presenting a range of topics to prepare PNs for their additional roles. Topics presented in the workshop include:

• Screening for depression;

• Identification and measurement of physiological risk factors such as high cholesterol, blood pressure, blood glucose and central obesity;

• Lifestyle risk factors such as smoking, poor nutrition, alcohol and physical inactivity;

• Training to educate patients in diabetes and heart disease risk reduction;

• Training in assisting patients with goal setting and problem solving;

• Coordinating referrals and timetabled follow up; and

• Preparing the draft GP Management Plan.

### Intervention programme

Each patient's session with the PN is scheduled to take approximately one hour. During their initial (baseline) session, each patient completes the SF36v2 questionnaire and a new PHQ-9 questionnaire if the earlier one is more than two weeks old. Their current medication list is also updated to include over-the-counter products. The PN assesses the patient, beginning by measuring their physiological parameters, reviews the potential risk factors (biological, lifestyle, psychological) and develops up to three lifestyle goals with the patient that he/she feels are achievable in reducing his/her risk factors. The SNAP (Smoking, Nutrition, Alcohol, Physical exercise) assessment , for example, can be a useful guide. The PN and patient identify possible barriers to achieving these goals and discuss enabling methods that may overcome these barriers. The PN may also suggest other professional services that may assist the patient in improving his/her outcomes, such as a dietician or counsellor. The PN may also supply educational material to assist patients in understanding their condition and meeting their goals. The PN completes the consultation by setting the review appointment date, and identifying any future tests that may be required beforehand. Patients responding positively to the ninth question on the PHQ-9, which assesses suicidal ideation, are immediately referred to their GP. The practice nurse consultation is scheduled to take about 45 minutes to complete. The remaining 15 minutes is set aside to add these data to the GP management plan (GPMP) before this is forwarded to the GP. The draft GPMP document becomes a readily accessible information support document for medication changes and referrals. The GP completes the plan during the consultation with the patient, providing the patient with a copy of the completed GPMP document.

An important aspect of this collaborative care programme is that patients are recalled systematically to monitor the progress of their care. Another important aim is that the nurse-led care can be completely self-funded using the normal Medicare item numbers. Consequently, a thirteen-week interval was chosen as the recall period. The recall visits are booked at the time of the previous visit. During each review, patients will complete a new PHQ-9 questionnaire so that any changes to their mental health can be monitored. Additional therapies or new strategies can be considered during the consultations if the PHQ-9 score has not improved by at least 50% or dropped below 5. These strategies may include changing or adding medication or referral to a mental health professional. The PN and patient then re-evaluate the goals from the previous consultation. In the second (6-month) and fourth (12-month) consultations, the patient will complete a new SF36v2 form to assess changes in quality of life.

### Data collection, verification and analysis

The research team includes a practice facilitator in each region to offer support to practice nurses and to monitor progress of the research programme. Monthly teleconference meetings are held to identify common issues and problems so that these can be addressed in a timely manner.

Data collection begins in the practice with the PNs entering patient data into their respective practice electronic databases, and then using these data to generate the GPMP for each patient. The GPMP includes a de-referenced, office-use-only summary table, shown in the Appendix, with the data that are relevant to the research. The PN copies the de-identified summary table from the practice database into a data-validation spreadsheet supplied by the GGT UDRH. The spreadsheet checks the GPMP summary table for completeness, consistency and accuracy. It highlights missing data and data that lie outside expected ranges that may be a result of typographical errors. These provide a warning to allow the PNs to recheck the data. Once verified, the PN forwards the validated GPMP summary data to the research team at GGT UDRH, where a final check is performed before their data are added to the master database. 

Independent groups *t*-tests and *χ*^2 ^tests will be used with baseline measures to check intervention and control for any imbalance. Clinical measures and changes (between baseline and follow-up) in outcomes of participants will be compared with measurements of controls. The difference in the change in the continuous outcome measures (particularly the PHQ-9 score) between the two studied groups will be analysed using linear mixed models, treating "group" as a between-subject factor and "time" as a within-subject factor. Categorical outcome variables will be analysed using generalised estimating equations (GEE), following the same approach. The intention-to-treat principle will be adhered to, and sensitivity analysis will also be carried out. Regression analysis, including logistic regression, will be used to identify baseline variables that predict successful outcomes and adherence.

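### The PHQ-9 analysis is stated as a difference in change with no baseline adjustment, which gives up precision at no saving, and the baseline imbalance tests ignore clustering

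*Protocol article*

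**What the plan says.** All of this is in the protocol article.

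- **Data collection, verification and analysis:** the contrast for continuous outcomes is "The difference in the change in the continuous outcome measures (particularly the PHQ-9 score) between the two studied groups". These outcomes "will be analysed using linear mixed models, treating 'group' as a between-subject factor and 'time' as a within-subject factor". No baseline covariate and no constraint on the baseline means is mentioned.
- **Same section, on baseline:** independent-groups t and chi-square "tests will be used with baseline measures to check intervention and control for any imbalance". The section does not say what follows from a significant result. Otherwise baseline variables enter only a separate regression for predictors of success and adherence.
- **Sample size:** "Nine intervention and nine control practices, each with 50 patients, will be required". The target is a difference of 2 points with 80% power and alpha 0.05. The calculation is made "assuming a change in PHQ-9 with standard deviation of 5.1 as observed in the pilot study", and it allows for drop-out of at most 33% and an intra-cluster correlation (ICC) of 0.04. The design is therefore powered on change, in line with the analysis.
- **Practice recruitment:** practices were added "until six practices from each of the three regions had been selected". The Randomisation section gives a 9:9 allocation and does not say whether it was restricted by region.

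**The concern.** If baseline is one level of the time factor and the arms may differ freely at baseline, the group-by-time contrast with complete data equals the difference in mean change. That contrast subtracts the whole baseline difference between arms, although only a fraction of it (r, under equal variances) would be expected to persist to follow-up. Adjustment removes only the predictable fraction. It is therefore never less precise in large samples, and it leaves almost no dependence on the baseline difference that happened to arise.

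This matters more than usual with nine practices per arm, because clustering widens the chance baseline differences between arms. What is at stake is the width of the confidence interval for the primary outcome, and an estimate that moves with the luck of the allocation.

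The imbalance tests are a separate weakness. They treat patients as independent, while the sample size calculation assumes that they are not. They would report imbalance too often, and they do nothing to the estimate.

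**Working it through.** **Inputs from the article.** Difference 2 points; SD of change 5.1; alpha 0.05 (taken as two-sided); power 80%; 9 practices per arm with 50 patients each; drop-out 33%; ICC 0.04.

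**Assumed, because the article does not give them.** Baseline to follow-up correlation r of 0.3, 0.5 and 0.7; the ratio k of baseline SD to follow-up SD, equal to 1 unless stated; the same ICC and correlation structure at baseline and follow-up.

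**1. The plan's own figure.** Independent patients per arm: 2 × (5.1 × (1.960 + 0.842) / 2)² = 102.07, rounded up to 103. Design effect: 1 + 49 × 0.04 = 2.96. Analysable per arm: 103 × 2.96 = 304.9. Enrolled per arm: 304.9 / 0.67 = 456 after rounding up, against 9 × 50 = 450. With 450 × 0.67 = 301.5 completers per arm the power is 79.9%. The stated size reproduces.

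**2. Precision.** Var(adjusted) / Var(change) = (1 − r²) / (1 + k² − 2rk). This never exceeds 1, because the denominator minus the numerator is (k − r)². At k = 1 it reduces to (1 + r) / 2.

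| r | k = 0.8 | k = 1 | k = 1.2 |
|---|---|---|---|
| 0.3 | 0.78 | 0.65 | 0.53 |
| 0.5 | 0.89 | 0.75 | 0.60 |
| 0.7 | 0.98 | 0.85 | 0.67 |

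A simulation with 18 practices, 33 completers each and ICC 0.04 gave 0.62, 0.75 and 0.84 at k = 1, close to theory. Interval width scales with the square root of the ratio: √0.65 = 0.81 and √0.85 = 0.92, so 8 to 19% narrower at k = 1 only.

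**3. Power for 2 points at the planned size, k = 1.** The residual SD is 5.1 × √((1 + r)/2).

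| Analysis | Residual SD | Normal approximation, design effect 2.96 | t with 16 df, design effect 2.30 |
|---|---|---|---|
| Change score | 5.10 | 79.9% | 84.6% |
| Adjusted, r = 0.3 | 4.11 | 93.5% | 95.8% |
| Adjusted, r = 0.5 | 4.42 | 89.8% | 93.0% |
| Adjusted, r = 0.7 | 4.70 | 85.9% | 89.8% |

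The third column follows the method that reproduces the plan. The fourth uses 33.5 completers per practice (1 + 32.5 × 0.04 = 2.30) and practice-level degrees of freedom.

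**4. Chance baseline difference.** At k = 1 each point of baseline difference shifts the change contrast by −(1 − r). Simulated slopes at r = 0.5 and 0.7 were −0.52 and −0.31 for change, and −0.02 and −0.01 after adjustment. An SD of change of 5.1 implies a baseline SD of 5.1 / √(2(1 − r)), which is 4.31, 5.10 and 6.58 for the three values of r. The SD of the chance difference between arms is that value × √(2 × 2.96 / 450), or 0.49, 0.58 and 0.76 points. Multiplied by (1 − r), the typical shift is 0.35, 0.29 and 0.23 points, against a target of 2. This is not a loss on top of step 2: it is where the extra variance comes from.

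**5. Baseline tests.** A nominal 5% patient-level test rejects under true balance with probability 2 × (1 − Φ(1.96 / √design effect)). With 50 per practice (2.96) this is 25.5%; with 33.5 per practice (2.30) it is 19.6%. Over ICCs of 0.01 to 0.05 and both practice sizes it runs from about 9% to 29%.

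**The case against.** The strongest reply is that nothing here is invalid. Under randomisation the difference in change is unbiased, the trial is powered on the SD of change, and the sample size matches that analysis. That stands: the issue is efficiency, together with an error that depends on the realised imbalance and averages zero over randomisation.

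The model sentence also does not fix whether the baseline means are free or common. A model with a common baseline mean would fit the same words and behave like an adjusted analysis. With drop-out allowed up to 33%, the equivalence to a change score is not exact either. This is fair. Free baseline means are the natural reading of a group-by-time model, but the text does not compel it, which is a reason to state the choice.

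The size of the gain depends on k as well as r. Selecting patients on a screening PHQ-9 above 5 may reduce baseline spread, and at k = 0.8 and r = 0.7 almost nothing is gained. The PHQ-9 is also repeated at the first session if the earlier form is over two weeks old, so for some patients part of the regression to the mean occurs before baseline. The direction holds; the range is an assumption.

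Four stronger readings are tempting, and the article does not support them:

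- *Chance imbalance in PHQ-9 is left in the estimate.* The change contrast subtracts it and over-corrects.
- *The baseline tests replace adjustment.* The article does not say so, and it promises sensitivity analyses that it does not list.
- *Omitting region is an error.* An unrestricted 9:9 draw would split all three regions 3:3 with probability C(6,3)³ / C(18,9) = 8000 / 48620 = 16.5%. But the article is silent on restriction, stratification terms may sit in a fuller document, and no between-region variance is given from which to compute an effect.
- *The sample size is wrong.* It reproduces.

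**Conclusion.** The point holds as an improvement available at negligible cost, not as a flaw that invalidates the analysis. As stated, the main analysis of PHQ-9 is most naturally a change-score contrast, which is less precise than one adjusted for a baseline value that the trial already collects. At k = 1 and r from 0.3 to 0.7, adjustment multiplies the variance by 0.65 to 0.85, and power at the planned size rises from 79.9% to between 85.9% and 93.5% by the plan's own method. Across k from 0.8 to 1.2 the variance ratio runs from 0.53 to 0.98. Neither r nor k is in the article, so only the direction is firm.

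The finding on the baseline tests does not depend on r or k. It needs only that the plan's ICC of 0.04 applies roughly to baseline variables, and it gives false flags for about 20 to 25% of truly balanced variables. It affects reporting and leaves the treatment estimate untouched.

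**What to change.** - Keep the linear mixed model, with practice as a random effect. Analyse follow-up PHQ-9 with baseline PHQ-9 as a covariate, or keep baseline among the outcomes and constrain its mean to be equal across arms. State which.
- Treat the other continuous outcomes in the same way.
- Drop the baseline t and chi-square tests and describe baseline characteristics by arm.
- As a secondary point, include region as a fixed effect, for example if allocation was stratified by region. This takes two practice-level degrees of freedom (16 to 14). With design effect 2.30 and k = 1, power would then be 95.5%, 92.6% and 89.2% for r = 0.3, 0.5 and 0.7, against 95.8%, 93.0% and 89.8% without it, before any gain from explaining regional variation.

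The cost is a change of analysis wording, made before outcome data are examined. No extra patients, visits or measurements are needed, and the stated sample size stays as it is.

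### Categorical outcomes go to GEE with only 18 randomised practices: clustered on practice but with ordinary uncorrected robust errors, false positives run at about 8–10% instead of 5%

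*Protocol article*

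**What the plan says.** The Methods/design section fixes the practice as the unit of allocation: "This study is a cluster-randomised intervention trial in which general practices were allocated either to an intervention group". Under Randomisation: "Nine practices were randomly allocated to the intervention group in which nurse-led collaborative care will be undertaken"; the other nine practices form the control group. The Sample size section allows for this with an intra-cluster correlation of 0.04.

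In Data collection, verification and analysis, continuous outcomes, chiefly the PHQ-9 score, are compared by linear mixed models, "treating 'group' as a between-subject factor and 'time' as a within-subject factor". For the rest: "Categorical outcome variables will be analysed using generalised estimating equations (GEE), following the same approach". Practice does not appear as a level, factor or cluster in either sentence. The section names no working correlation, variance estimator, reference distribution or small-sample adjustment for the GEE.

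**The concern.** The usual GEE robust (sandwich) variance is justified by a large number of independent clusters. In this trial the independent units are practices, and there are nine in each arm. With so few, the uncorrected sandwich underestimates the variance, because residuals are taken about arm means fitted from the same few practices. A normal reference also ignores that the variance is estimated on only 16 degrees of freedom. Both errors make p-values too small.

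This is distinct from the absence of a practice term. An analyst who notices the omission and simply declares practice as the cluster removes the larger error but keeps this one.

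At stake are significance statements and intervals for categorical results. The article does not list its categorical outcomes. Candidates from the Appendix are smoking, exercise, antidepressant use and mental-health referral. The 50% PHQ-9 reduction in the Objectives would join them if it were analysed as a responder outcome, which the article does not say.

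**Working it through.** **Inputs from the article.** 9 + 9 practices; 50 patients each; SD of PHQ-9 change 5.1; difference 2 points; intra-cluster correlation (ICC) 0.04; drop-out up to 33%, so 50 × 0.67 ≈ 33 analysed per practice; significance level 0.05 (taken as two-sided) and 80% power.

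**Assumptions, because the article gives no figures.** ICC 0.04 also applies to binary outcomes; prevalence 10–50%; variation in analysed practice size, as a coefficient of variation (CV), from 0 to 0.6.

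**1. The plan's own figure.** Unclustered size per arm: 2 × (1.96 + 0.842)² × 5.1² / 2² = 102.1, rounded up to 103. Design effect: 1 + (50 − 1) × 0.04 = 2.96. Then 103 × 2.96 = 305, and 305 / 0.67 = 455.2, rounded up to 456, against 9 × 50 = 450 in the plan. The sample size reproduces to within 1.3%, so clustering was taken into account at the design stage.

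**2. Practice as cluster, uncorrected sandwich, normal reference: closed form.** With k equal-sized practices per arm, the sandwich variance is too small by (k − 1)/k, on 2(k − 1) degrees of freedom. The false-positive rate is 2 × P(t₂₍ₖ₋₁₎ > 1.96 × √((k − 1)/k)).
- k = 9: 2 × P(t₁₆ > 1.96 × √(8/9)) = **8.3%**
- k = 7: 9.5%
- k = 6: 10.4%

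**3. The same analysis by simulation, no true effect.** Beta-binomial practices, logit GEE with independence working correlation, single follow-up, 40,000 trials per setting, ICC 0.04:

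| Practice sizes | Uncorrected, normal reference |
|---|---|
| Equal | 8.0–8.7% |
| CV 0.3 | 8.4–9.5% |
| CV 0.6 | 10.1–11.0% |

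A second simulation fitted GEE with an exchangeable working correlation (3,000 trials per setting). It gave 7.8% with equal sizes, 9.1% at CV 0.5, and 8.2% for the group-by-time term that the article's model implies. Over ICC 0.01–0.10 and prevalence 10–50%, the first simulation ranged from 7.8% to 12.5%.

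**4. Practice ignored (the sentence read literally).** With 33 analysed patients per practice the design effect is 1 + 32 × 0.04 = 2.28, so the test statistic is inflated by √2.28 = 1.51. The rate is 2 × P(Z > 1.96/1.51) = 19.4%. Simulation at ICC 0.04 gave about 19–30%.

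**5. With a correction (practice as cluster, ICC 0.04).**

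| Variance and reference | False-positive rate |
|---|---|
| Uncorrected, t₁₆ | 6.1–8.7% |
| Kauermann-Carroll, t₁₆ | 4.7–6.5% |
| Mancl-DeRouen, normal | 5.1–6.4% |
| Mancl-DeRouen, t₁₆ | 3.7–4.7% |

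Changing the reference distribution alone is not enough; the variance needs correcting too.

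**6. Cost in interval width, equal sizes.** t₁₆ against normal: 2.120/1.96 = 1.082. Kauermann-Carroll: √(9/8) × 1.082 = 1.147, about 15% wider. Mancl-DeRouen: (9/8) × 1.082 = 1.217, about 22% wider.

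**The case against.** The strongest reply is that the article does not commit to the analysis that gives 8–10%. It names GEE and nothing more: no robust z-test is stated and no correction is excluded. GEE with a corrected sandwich and a t reference fits the quoted sentence and holds about 5%. Such detail is often left to an analysis plan, which is not shown here. It can be added that, taken at its word, the sentence makes the patient the GEE unit; there are then hundreds of units, and the fault is the omitted practice level, not the small number of clusters.

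Much of this stands. A reader might infer that the plan fixes an 8–10% error rate; the text does not support that, and the figure is conditional. What remains is that neither obvious reading is safe. The literal sentence gives about 20% or more, and ordinary GEE after the obvious repair gives about 8–10%. Only a version with a specific correction holds the level, and nothing in the analysis section points to one.

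Two other inferences should be resisted. One is that the primary result is affected: the article sends the PHQ-9 score to linear mixed models. The other is that those mixed models share the fault through large-sample tests: the article says only that the difference in change "between the two studied groups will be analysed using linear mixed models" and gives no estimation method, test or degrees of freedom, so no error rate can be attributed to them.

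The figures for uneven practice sizes and lost practices also rest on assumptions. The article aims for 50 patients in every practice and anticipates no loss of practices.

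**Conclusion.** The concern holds in conditional form and for categorical, non-primary outcomes only. With 18 practices, GEE clustered on practice with uncorrected robust errors and a normal reference has a false-positive rate of about 8–10% at a nominal 5%. The rate is 8.3% in closed form for equal practices and passes 10% when sizes vary strongly or only six practices per arm remain. If practice is left out, it is about 20% or more.

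The result rests on borrowing ICC 0.04 for binary outcomes, on about 33 analysed patients per practice and on prevalence of 10–50%. The 8.3% depends little on the ICC or prevalence, since it follows mainly from having nine practices per arm. The figure for ignoring practice depends directly on the ICC. It is worth correcting before analysis, but it does not threaten the primary comparison.

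**What to change.** Replace the GEE sentence with wording such as:

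> Categorical outcomes will be analysed by GEE with practice as the cluster, a Kauermann-Carroll small-sample-corrected sandwich variance and t tests on 16 degrees of freedom (number of practices minus 2), or by an equivalent practice-level analysis.

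If practices are lost, the degrees of freedom follow the number analysed. Settle the choice before outcome data are examined.

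The change needs no new data, only a sentence and a software option. The price is confidence intervals about 15% wider than those from uncorrected GEE clustered on practice, and correspondingly fewer nominally significant results. Mancl-DeRouen with the same t reference is also defensible, but it widens intervals by about 22% and is somewhat conservative (3.7–4.7%), so the two are not interchangeable and one should be named.
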